### Cost-effectiveness

As part of the ENRICHED trial, a cost-effectiveness analysis will be performed, focusing on formal care costs over a period of 12 months. These costs will include routine costs of standard perioperative care, intervention costs (eg, protein supplementation, RT equipment and personnel) and general healthcare consumption costs. Healthcare consumption will be assessed using extracted data from the electronic patient records, supplemented by selected items from the iMTA Medical Consumption Questionnaire.^37^ Additionally, HRQoL will be assessed using the EQ-5D-5L questionnaire.^32^ The incremental costs between the intervention and standard care will be related to the difference in proportion of patients achieving the success criterion defined as FFML/TWL ≥30% at 12 months.

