**Methods and analysis:**

In the EffectiveNess of pRotein supplementatIon Combined witH resistance Exercise training to counteract Disproportional fat-free mass loss following metabolic bariatric surgery (ENRICHED) randomised controlled trial, 400 patients scheduled to undergo MBS will be randomised in a 1:1 ratio to the ENRICHED perioperative care programme (intervention group) or the standard perioperative care programme of the Dutch Obesity Clinic (control group). The study is currently recruiting participants at two centres in the Netherlands: Nieuwegein and Amsterdam. The postoperative standard programme consists of 13 group sessions spread over a period of 18 months. As part of the ENRICHED programme, RT and protein supplementation will be added 3 weeks after MBS. Additional whole-body RT consists of home-based training sessions two to three times a week, and supervised RT sessions of 45–60 min once weekly, performed at 60–75% of one-repetition maximum (1-RM). Protein supplementation will start by adding 20 g of whey protein to the daily intake. The supplementation will be gradually increased with 20 g every 4 weeks until a total of 60 g whey protein a day is reached. After 12 weeks of protein supplementation, the focus shifts towards incorporating protein-rich food products into the daily dietary intake. The primary endpoint is the prevalence of disproportional FFM loss, defined as FFML/total weight loss ≥30%, at 3 months post-MBS. Secondary endpoints are differences in body composition, muscle strength and function, cardiorespiratory fitness, (cardio)metabolic health, health-related quality of life, gastrointestinal discomfort, cost-effectiveness of the intervention and treatment satisfaction. Outcomes will be assessed preoperatively and at 3, 6 and 12 months postoperatively.

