## Introduction

 Obesity has become a pressing global health challenge, with its prevalence and severity continuing to rise across populations worldwide.^1^ Metabolic–bariatric surgery (MBS) is one of the most effective long-term interventions for the treatment of severe obesity, with a total weight loss (TWL) around 30% at 12 months postsurgery.^2^ In addition to weight reduction, MBS has been shown to be effective in improving metabolic health and reducing obesity-associated complications, thereby enhancing overall health-related quality of life (HRQoL).^3 4^

Despite these benefits, weight loss following MBS comprises not only fat mass (FM) but also a considerable proportion of fat-free mass (FFM). Studies have shown that approximately 25% of the TWL within the first 3 months post-MBS consists of FFM.^5^ FFM plays a crucial role in key physiological functions, including glucose metabolism, resting energy expenditure, thermoregulation and physical capacity.^6^ In turn, disproportional loss of FFM has been associated with impaired metabolic health and functional capacity, and an increased risk for chronic diseases ultimately leading to lower HRQoL.^47^,^9^ In the present study, we define a proportion of FFM loss (FFML) ≥30% as disproportional, based on previous evidence linking this ratio of FFML/TWL to an increased risk of major adverse cardiovascular events and mortality.^10^ The insights in the health consequences of FFML have shifted treatment goals in obesity treatment, coming from maximising weight loss to improving body composition and thereby general health.^11^

Resistance training (RT) complemented with protein supplementation has been shown to be effective for maintaining and improving FFM in healthy^12^ and clinical populations.^13^ However, patients post-MBS often fail to meet the daily recommended protein intake of 60 g/day^14^ and physical activity (PA) levels of 150 min of moderate-intensity PA.^15 16^ Evidence of the effectiveness of RT and protein supplementation in the early postoperative phase (3–12 months) following MBS remains limited. Previous studies have been rather small and involved homogeneous populations,^17^ or have focused solely on the late postoperative period (2–7 years post-MBS), with inconsistent findings.^18 19^

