### Outcome measures

The primary outcome is the difference in proportion of patients with disproportional FFML/TWL (ie, ≥30%) in the intervention group compared with the control group at 3 months post-MBS. Secondary outcomes are postintervention differences in body composition, muscle strength and function, cardiorespiratory fitness, (cardio)metabolic health, HRQoL, gastrointestinal discomfort, cost-effectiveness of the intervention and treatment satisfaction in the intervention group. Most outcomes are measured preoperatively and at 3, 6 and 12 months post-MBS. Cost data are assessed preoperatively and at 6 and 12 months post MBS, and treatment satisfaction is assessed after the 6-month intervention period. Cost and outcome data are used to calculate the incremental cost-effectiveness of the intervention in terms of cost per successfully treated patient using a time horizon of 1 year.

The primary outcome was set at 3 months post-MBS as previous studies have shown that the most pronounced changes in body composition, including substantial reduction in FFM, occur during this early postoperative phase.^5 23^ Our intervention, combining RT and protein supplementation, was specifically designed to target this critical period. Secondary outcomes will be assessed at 6 and 12 months to assess the persistence of potential effects over time.

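### The cost-effectiveness success criterion (FFML/TWL ≥30%) is the trial's adverse outcome, so applied as written the cost per success has the wrong sign

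*Protocol article*

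**What the plan says.** The Cost-effectiveness section fixes the effect measure of the economic analysis. Incremental costs are set against this quantity: "difference in proportion of patients achieving the success criterion defined as FFML/TWL ≥30% at 12 months". The Outcome measures section names the resulting ratio as "cost per successfully treated patient using a time horizon of 1 year".

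The same cut-off, in the same direction, is defined elsewhere in the article as the outcome to be avoided:

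- Introduction: "we define a proportion of FFM loss (FFML) ≥30% as disproportional, based on previous evidence linking this ratio of FFML/TWL to an increased risk". The risk named there is of major adverse cardiovascular events and mortality.
- Abstract: "The primary endpoint is the prevalence of disproportional FFM loss, defined as FFML/total weight loss ≥30%, at 3 months post-MBS".
- Outcome measures, on what the trial is chiefly judged by: "difference in proportion of patients with disproportional FFML/TWL (ie, ≥30%) in the intervention group compared with the control group at 3 months post-MBS".
- Sample size: the intervention counts as successful if the prevalence of disproportional loss is 14%, against 26% in the control group.

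**The concern.** The article uses the idea of success in two opposite ways. In the Sample size section, success means fewer patients at or above 30%. In the Cost-effectiveness section, success for a patient means being at or above 30%. Both cannot stand.

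The direction of the incremental cost-effectiveness ratio is at stake. If an analyst programs the criterion as written, an intervention that prevents disproportional loss produces fewer successes than standard care. If it also costs more, it is reported as dominated. An intervention that increased disproportional loss would appear to buy successes. The Discussion says the economic analysis is meant to inform implementation in routine care, so a reversed ratio would point that decision the wrong way.

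**Working it through.** **Inputs**

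- Prevalence of FFML/TWL ≥30%: control 0.26, intervention 0.14 (Sample size). These are 3-month planning values. The article gives no 12-month values, so using them at 12 months is an assumption.
- Two-sided α = 0.05, power 80%, 174 per arm (Sample size).
- Incremental cost per patient, ΔC: not given in the article. Assumed values of EUR 500, 1,000 and 2,000 are used to show a range.

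**Step 1. Reproduce the plan's own figure, to confirm which direction the design takes as favourable.**

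With pooled variance under the null and no continuity correction:

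n per arm = [z₀.₉₇₅ √(2·p̄·(1−p̄)) + z₀.₈₀ √(p₁(1−p₁) + p₂(1−p₂))]² / (p₁−p₂)²

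- p̄ = (0.26 + 0.14)/2 = 0.20, so 2 × 0.20 × 0.80 = 0.3200.
- 0.26 × 0.74 + 0.14 × 0.86 = 0.1924 + 0.1204 = 0.3128.
- n = [1.960 × √0.3200 + 0.842 × √0.3128]² / 0.12² ≈ 173.2, rounded up to 174.

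This matches the stated 174 per arm. Allowing for 10% drop-out, 174/0.9 gives 194 per arm, which the planned 200 covers. The design therefore treats ≥30% as the event to be reduced.

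**Step 2. Effect difference under each definition of success (intervention minus control).**

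| Success defined as | Control | Intervention | ΔE |
|---|---|---|---|
| FFML/TWL ≥30% (as written) | 0.26 | 0.14 | 0.14 − 0.26 = −0.12 |
| FFML/TWL <30% (complement) | 1 − 0.26 = 0.74 | 1 − 0.14 = 0.86 | 0.86 − 0.74 = +0.12 |

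In general (1 − p_I) − (1 − p_C) = −(p_I − p_C). The size is the same and the sign is opposite, whatever the true rates.

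**Step 3. Ratio = ΔC / ΔE.**

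| Assumed ΔC (EUR per patient) | As written | With <30% |
|---|---|---|
| 500 | 500/(−0.12) = −4,167 | 500/0.12 = +4,167 |
| 1,000 | 1,000/(−0.12) = −8,333 | 1,000/0.12 = +8,333 |
| 2,000 | 2,000/(−0.12) = −16,667 | 2,000/0.12 = +16,667 |

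With positive ΔC, the criterion as written places an effective intervention among results that cost more and achieve less. The complement gives a positive cost per additional patient successfully treated.

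**Step 4. Look for a reading that removes the conflict.** The later time point does not explain it: the stated aim is to counteract disproportional loss over months 3 to 12, so ≥30% is still unfavourable at 12 months. The article gives no other definition of success.

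**The case against.** The strongest reply is that this is probably a reversed inequality sign and that the intended direction is clear from the rest of the article. An analyst would have to overlook the Introduction, the primary outcome and the sample size to report an effective intervention as dominated. It can also be said that the section gives no order of subtraction. Control minus intervention on the ≥30% proportion gives +12 points, a legitimate cost per case of disproportional loss avoided.

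The first part is fair as to likelihood, but it does not make the stated definition right. The second part does not fit the text, which counts patients who achieve a success criterion and names the result as a cost per successfully treated patient. Neither phrase describes cases avoided.

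Three limits do stand:

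- Cost-effectiveness is a secondary outcome. The primary endpoint, the sample size and the data collected are untouched, and the criterion can be recomputed from the 12-month measurements.
- The Discussion also mentions quality-adjusted life years, and the EQ-5D-5L is collected. A ratio on that scale would keep its direction. The cost per success is nevertheless the ratio that the Outcome measures and Cost-effectiveness sections spell out.
- The euro figures are illustrations, and the label dominated requires the intervention to cost more than standard care.

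**Conclusion.** The concern holds: the criterion is wrong as written. The Cost-effectiveness section defines success as the state that the rest of the article defines as failure. Applied literally as intervention minus control, it reverses the effect difference exactly: −12 instead of +12 percentage points at the planning rates, and −EUR 8,333 instead of +EUR 8,333 per additional success at an assumed extra cost of EUR 1,000. The amounts rest on that assumed cost and on carrying 3-month rates to 12 months. The reversal rests on neither, and holds for any non-zero differences in cost and effect. The error is confined to the cost-per-success ratio, but it is in a prespecified outcome definition and must be corrected.

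**What to change.** In the Cost-effectiveness section, define success as FFML/TWL below 30% at 12 months and state the ratio in full:

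(mean cost, intervention − mean cost, control) / (proportion <30%, intervention − proportion <30%, control)

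This agrees with the cost per successfully treated patient named under Outcome measures. An equivalent alternative is to keep ≥30%, drop the word success, and report cost per case of disproportional loss avoided, with the effect taken as control minus intervention. That would also require rewording the Outcome measures section, so the first option is simpler. Any separate health-economic analysis plan should carry the same definition.

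The change is one line and needs no new data, patients or visits. Recruitment is expected to run until December 2026, so the correction can be documented before the 12-month results are analysed. Made after the results are known, it could look like a post hoc choice.

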### Patient and public involvement

Patients and healthcare professionals were involved in the design of the ENRICHED protocol and the practical implementation of the intervention in the NOK clinics through focus group interviews. Two separate focus groups were held during the design phase of the study protocol. For these group sessions, patients and healthcare professionals (eg, dieticians, kinesiologists, psychologists and bariatric physicians) were invited to participate in a semistructured group discussion, aimed at gathering input on the feasibility of the intervention and to identify any potential challenges and barriers. The insights gained from these sessions were incorporated into the development of the study protocol. This approach to engage relevant stakeholders aimed to ensure that the intervention is not only evidence-based but also tailored to meet the practical needs in a real-world clinical setting.

## Ethics and dissemination

This study protocol has been developed in accordance with the Standard Protocol Items: Recommendations for Interventional Trials 2025 statement^38^ and has been reviewed and approved by the Medical Research Ethics Committee Oost-Nederland (NL-OMON57119). Any substantial amendments to the protocol will be submitted for ethical approval prior to implementation. Written informed consent will be obtained from all participants prior to enrolment (see online supplemental material for the informed consent form). Participants will be informed of the possibility to withdraw from the study at any time without consequences. The results of the ENRICHED trial will be disseminated in line with the Consolidated Standards of Reporting Trials 2025 statement^39^ through peer-reviewed scientific journals and presentations at national and international conferences. Data will be shared on reasonable request after publication of the main trial results.

### Monitoring

Given the negligible risk associated with this study, no formal data monitoring committee has been established. However, an independent monitor has been appointed to verify the informed consent procedure shortly after study initiation and conduct interim on-site visits to review data entry and reported serious adverse events and suspected unexpected serious adverse reactions. On study completion, the monitor will perform a close-out visit to ensure proper closure and documentation.

## Discussion

While MBS is highly effective for achieving substantial and sustained weight loss, the need to preserve FFM post-MBS is often overlooked. Disproportionate FFML has been associated with impaired metabolic function, reduced physical capacity and increased risk of chronic diseases such as type 2 diabetes and cardiovascular diseases.^4^,^69 40^ However, only a few studies have evaluated strategies to mitigate FFML in the early postoperative phase following MBS. The ENRICHED trial is designed to address these gaps by evaluating the effectiveness of an intervention combining RT and whey protein supplementation on FFML, body composition, muscle strength and function, cardiorespiratory fitness, (cardio)metabolic health, HRQoL, gastrointestinal discomfort and cost-effectiveness of the intervention.

The intervention includes both supervised and home-based RT sessions, tailored to the participants’ capacity and progression. The use of the Technogym application introduces real-time tracking of training frequency and intensity. In addition, habitual PA will be objectively assessed using accelerometry in a subgroup, enabling detailed analysis of daily activity patterns and potential dose–response relationships.

Previous studies investigating RT and protein supplementation post-MBS have shown mixed results, often limited by a small or specific sample size, or mid to long-term follow-up only.^17^,^19^ For example, one RCT reported improved muscle strength in the group receiving RT and protein supplementation, but no effect on lean body mass at 6 months post-MBS. This trial was limited by a relatively small sample size (n=76), and a homogeneous study population (eg, exclusively women undergoing RYGB), limiting the generalisability of the findings.^17^ Another study did find a positive association between a combined intervention of RT and protein supplementation and increased FFM and skeletal muscle mass, but this study focused on the long-term follow-up (2–7 years), rather than the early postoperative period when FFML is most pronounced.^19^ In other studies, focusing exclusively on RT or protein supplementation post-MBS, the absence of a combined intervention limits the ability to assess potential synergistic effects on FFM preservation.^1641^,^43^ The ENRICHED trial addresses these limitations by including a larger and more general population (ie, both men and women, undergoing either RYGB or SG), and by focusing on the early postoperative period.

Limitations observed in previous studies have been low compliance to protein intake protocols, potentially due to gastrointestinal discomfort and lacking information on habitual PA patterns.^43^ The protein supplementation protocol in the ENRICHED trial is based on recent findings that consumption of whey protein resulted in the highest increase in overall daily protein intake, compared with other types of protein supplementation strategies.^44^ Additionally, whey protein was found superior to other types of protein, such as soy, casein or hydrolysed collagen proteins, to increase muscle protein synthesis.^45^ Adherence to the ENRICHED protocol is closely monitored, enhancing the interpretation of the true effect of the intervention. Moreover, the intervention is embedded in the standard perioperative care programme.

In addition to clinical outcomes, the ENRICHED trial includes a cost-effectiveness analysis to evaluate the economic impact of the intervention. By combining quality-adjusted life years (QALYs) with data on healthcare consumption costs, this analysis will provide valuable insights into the potential for the implementation of the intervention in routine care.

The present study could have several strengths, including its multicentre design, large sample size and implementation of the intervention into a routine clinical setting. However, some limitations should be acknowledged. First, blinding of participants and care providers is not possible due to the nature of the intervention, which may introduce performance bias. Second, although DXA measurements are considered the gold standard for body composition assessment, it is not always feasible for repeated use due to cost, limited availability and radiation exposure. BIA, although validated, may be less precise. Finally, adherence to both RT and protein intake may vary, despite monitoring and counselling, which may influence outcomes.

The ENRICHED trial will implement an innovative protocol combining home-based and supervised RT complemented with whey protein supplementation to improve postoperative outcomes in patients undergoing MBS. Application of evidence-based dietary and RT strategies with accurate monitoring in a real-world clinical setting can potentially contribute to revision of standard clinical care guidelines for a patient-tailored intervention for the preservation of FFM.
